### Sampling

3.2

Since the study is focused on saliva samples, subjects with severe hypo-salivation at the first sampling (saliva flow rate at baseline <0.1 mL min^−1^), because of their inability to dissolve the tablet formulation, will be rolled out. Saliva production will be determined by the spit method at baseline (*t* = 0) and after 7 days of treatment (*t* = 1) with Salifluss^TM^ twice a day or placebo.

The participants will be asked to avoid oral hygiene practices including flossing, brushing, and mouth-rinses as well as eating, and drinking for at least 2 hours before collection. Before sampling, the mouth will be rinsed with water for 2 minutes, and the subject will be asked to wait for 10 minutes.

The saliva samples will be obtained in the morning (8.00 am–10.00 am) according to the circadian rhythms in salivary flow.^[11]^ The unstimulated saliva samples will be collected by expectorating into sterile 50 mL tubes every 30 seconds. for 5 minutes as described earlier.^[12]^ The stimulated saliva will be collected in the same way after 2 minutes of chewing a paraffin wax ball.

The samples collected by an operator unaware of clinical data will be weighted, the pH will be measured by a pH-sensitive electrode, then centrifuged at 5000 *g* for 10 min at 4°C; the obtained supernatants will be supplemented with EDTA-free Protease Inhibitor Mixture (Sigma–Aldrich, Dorset, UK) and stored al −80° for the QP analysis. The collected samples will be analyzed at the Department of Pharmaceutical Sciences “Pietro Pratesi,” University of Milan, Milan, Italy (DISFARM) research laboratory.

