### Statistical analysis

3.5

Descriptive statistics of continuous variables understudy will be presented as mean ± SD; categorical variables were expressed as absolute numbers and percentages. The differences in continuous variables will be assessed using the Mann–Whitney *U* test when not normally distributed, and the Student *t* test when normally distributed. The *X*^2^ test was used to test for differences in categorical variables. The relationship between all variables before and after active/placebo treatment will be tested by Spearman correlation coefficients and their 95% confidence intervals.

The primary outcome variable is the treatment-related change in any of the Sal parameter understudy, before and after active/placebo treatment in Cs/Ds subjects by intention to treat criteria, that is, including all patients with adequate sampling before and after treatment (7 days). Differences in treatment-related changes between the groups will be analyzed in the context of covariance analyses (ANCOVA), which included terms for treatment and baseline values as covariates. Treatment effects were assessed by the least-squares mean change from the above ANCOVA model.

If relevant, the intra- and inter-observer variability of sampling, as well as measurements, a repetition of sampling and data analysis will be performed. For intra-observer variability the primary observer will sample/analyze the data on 2 different days; for inter-observer variability the sample/analysis will be performed, independently, by a second observer who was blinded to previous results. Intra- and inter-observer variability will be calculated as the coefficient of variance, which is the standard deviation of the difference between observations divided by their mean and multiplied by 100.

The size of the sample and the power will be calculated expecting a type I error rate of 5% or less. When appropriate, a value of *P* < .05 will be considered significant.

If samples are missing for any cause (eg, not compliance with the trial protocol, no follow-up, others) they will be removed from the analysis.

Data will be analyzed at the end of the study when all samples will be collected. Access to the data in anonymized mode will be provided to the investigators.

A computer statistical package will be used to validate the model and to perform the analysis (SPSS v.20, IBM, Armonk, New York, USA).

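### The observer-variability formula omits the division by √2, so it overstates the within-subject CV by 41% under the usual error model; re-collection on two days adds the subject's own variation

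*Protocol article*

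**What the plan says.** Section 3.5 (Statistical analysis) of the protocol article foresees a reliability assessment under a condition: "If relevant, the intra- and inter-observer variability of sampling, as well as measurements". For this, "a repetition of sampling and data analysis will be performed". The intra-observer part reads: "For intra-observer variability the primary observer will sample/analyze the data on 2 different days". The inter-observer part reads: "for inter-observer variability the sample/analysis will be performed, independently, by a second observer who was blinded to previous results". Both results are to be expressed as one index, called the coefficient of variance and defined as the quantity "which is the standard deviation of the difference between observations divided by their mean and multiplied by 100".

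Section 3.2 (Sampling) shows what a repeated collection involves. "The unstimulated saliva samples will be collected by expectorating into sterile 50 mL tubes every 30 seconds", over 5 minutes, so a second flow measurement needs a second collection from the subject. The hour of collection is fixed: "The saliva samples will be obtained in the morning (8.00 am–10.00 am) according to the circadian rhythms in salivary flow". The article gives no observer SD, no day-to-day SD and no numerical result for observer variability.

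**The concern.** A coefficient of variation relates the SD of a single measurement to its mean. The formula puts the SD of a difference between two measurements in the numerator, and that is a larger quantity. A reader who compares the result with a coefficient of variation from elsewhere would think the measurements less precise than they are.

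The formula also ignores a constant offset. If one observer always reads higher than the other, the SD of the differences does not change, so the index is silent on that part of the disagreement.

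The design raises a separate question. If the same observer collects saliva on two days, the two values differ partly because the subject differs. Fixing the hour of collection controls time of day, not the day.

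Finally, a ratio to the mean suits pH poorly, because pH is a logarithmic scale with an arbitrary zero.

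What is at stake is the precision reported for flow and pH, which are among the saliva parameters that form the primary outcome. The treatment comparison itself is not affected.

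**Working it through.** The article states no figure for observer variability, so there is none to reproduce. The check applies its formula to known error sizes. All SDs below are assumptions, with the mean reading set to 1.

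**1. The factor √2.** Take two readings with independent errors of equal SD s and no systematic shift.
- Var(x₁ − x₂) = 2s², so SD of the difference = √2 × s.
- Article's index = 100 × √2 × s / mean. Within-subject CV = 100 × s / mean. Ratio = √2 = 1.414.
- With s = 0.10: the index is 100 × 1.414 × 0.10 = 14.1%, against a true 10.0%. A simulation of 400,000 pairs gave the same two values.

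**2. Dependence on independent errors.** If the two errors have correlation ρ, the ratio to the single-reading SD is √(2(1 − ρ)): 1.22 at ρ = 0.25 and 1.00 at ρ = 0.5.

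**3. Systematic shift b between readings.** The comparison is with a CV that includes the shift, 100 × √(mean(d²)/2) / mean, where mean(d²) = 2s² + b². With s = 0.10:

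| Shift b | Mean of readings | Article's index | CV including shift | Ratio |
|---|---|---|---|---|
| 0 | 1.00 | 14.1% | 10.0% | 1.41 |
| 0.10 | 1.05 | 0.1414/1.05 = 13.5% | √0.015/1.05 = 11.7% | 1.15 |
| 0.20 | 1.10 | 0.1414/1.10 = 12.9% | √0.030/1.10 = 15.7% | 0.82 |

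With a large enough shift the index understates total disagreement.

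**4. Re-collection on two days.** Let s_e be the observer SD and s_day the subject's day-to-day SD. Then SD of the difference = √(2(s_e² + s_day²)). With s_e = 0.10:

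| Assumed s_day | Article's index | After division by √2 | Observer CV |
|---|---|---|---|
| 0.05 | √0.025 = 15.8% | √0.0125 = 11.2% | 10% |
| 0.10 | √0.040 = 20.0% | √0.020 = 14.1% | 10% |
| 0.20 | √0.100 = 31.6% | √0.050 = 22.4% | 10% |

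Dividing by √2 does not remove the day component. That has to be separated by design or by reporting.

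**5. pH.** Assume a single-reading SD of 0.2 units at pH 7. The SD of differences is 1.414 × 0.2 = 0.283, and the article's index is 100 × 0.283 / 7 = 4.0%. Yet 0.2 units is a factor of 10^0.2 = 1.58 in hydrogen ion concentration. The small percentage comes from dividing by 7 and says little about precision.

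**The case against.** The strongest reply is that little depends on this. The assessment is to be done only if relevant, and no result in the article is miscalculated. The formula is also spelled out, so a reader can divide by √2. That stands, and it sets the severity.

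The second reply is that the stated target includes variability of sampling as well as of measurement, and that this can be seen only by collecting again. That also stands: re-reading one sample cannot replace re-sampling. In addition, "the primary observer will sample/analyze the data on 2 different days" can cover re-analysis of an existing sample or data set, where no subject variation enters. The day effect therefore applies only where saliva is re-collected.

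A reader might also infer more than the article supports:
- **That the inter-observer figure is free of subject variation, so the two figures cannot be compared.** The article gives no timing for the second observer. If that observer also collects afresh, subject variation enters there too.
- **That the divisor could be the mean difference, near zero.** The plural pronoun refers to the observations, so the sentence is clear enough.
- **That a repeat day may fall after the first tablet and pick up a treatment effect.** Nothing in the article places a repeat day there.
- **That 41% holds without conditions.** It needs independent, equal-variance errors and no systematic shift.

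**Conclusion.** The point holds as a minor one. The index named as a coefficient of variation is √2 times the within-subject CV, an overstatement of 41% (10% reported as 14.1%), if errors are independent, of equal variance and without systematic shift. It also omits any systematic difference between readings; with an assumed shift of 20% and an observer CV of 10%, it falls to 0.82 of a CV that counts the shift. It is therefore not established that the index always makes precision look too poor.

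Where saliva is re-collected on two days, the intra-observer figure mixes observer error with the subject's day-to-day variation. Its size cannot be derived from the article; the range above (index of 15.8% to 31.6% for an observer CV of 10%) rests on assumed day-to-day SDs of half to twice the observer SD.

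A reader might infer that the treatment effect or the power is compromised. The article does not support that: the index feeds neither the ANCOVA nor the sample size.

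**What to change.** Reword the reliability paragraph of section 3.5:
- **Flow:** CV = SD of the paired differences / √2 / mean of all readings × 100, with the mean difference between readings reported beside it.
- **pH:** within-subject SD in pH units (SD of the differences / √2), with limits of agreement, instead of a percentage of the mean.
- **Design:** report re-reading or re-analysis of the same sample (observer error) separately from re-sampling on another day (observer plus subject variation). Keep both, since the stated aim covers sampling as well as measurement, and say which of the two each reported figure represents.

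The formula changes cost only wording, because they use the same paired readings. Separate reporting costs a second reading of some samples if only re-collection had been intended. The article says the study has not started, so the change can be made before any data exist.

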## Discussion

4

From this study, we do expect to elucidate the mutual relationship between Sal characteristics and OM and to compare them with OD; furthermore, using specific bioinformatics tools to analyze the data, before and after treatment with Car, we are looking to see its potentials on preventing/treating OD and, using QP, eventually elucidate the mechanism of Car supplementation.

The study is not yet started, no related publications containing the results of this study have already been published or submitted to any journal; the results of the trial will be shared only by scientific publication.
